#### Statistical analysis plan for secondary outcomes

Secondary aims which compare NFN+ to NFN mothers related to a) consumption of fruits and vegetables and b) utilization of the Brighter Future Family Centers will be analyzed similar to the primary hypotheses. For the comparison of weight for length *z-*score between NFN+ and NFN infants, weight categories based on weight for length percentiles will be compared using chi-square analysis.

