**Methods/Design:**

Six family centers located in low-income neighborhoods in Hartford, CT were randomized into control and intervention neighborhoods. Fifty-seven mothers were recruited either prenatally or shortly after delivery into the Nurturing Families Network home visitation program; 27 lived in a control neighborhood and received the standard home visitation program and 30 lived in an intervention neighborhood and received both the standard home visitation program and the ECHO intervention. The intervention increases maternal skills in goal-setting, stimulus control and problem-solving, engages family members to support changes, links mothers to neighborhood resources and is embedded in the standard home visitation program. ECHO targets include breastfeeding, solids, juice and sugar-sweetened beverages, routines for sleep and responding to infant cues, television/screen time, and maternal diet and physical activity. We hypothesize that infants in ECHO will have been breastfed longer and exclusively, will have delayed introduction of solids and juice, have longer sleep duration, decreased television/screen time and a lower weight for length *z*-score at 12 months, and their mothers will have greater fruit and vegetable consumption and higher levels of physical activity.

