We hypothesized that at 6 and 12 months, as compared to NFN infants, NFN+ infants would have been breastfed longer and more often exclusively, would drink less sugar-sweetened beverages/juice, would have begun to ingest solids at an older age, and would sleep more hours/day, have more established sleep/wake routines, greater soothability and have fewer hours of television viewing/day. Secondary hypotheses of the study included that at 6 and 12 months, as compared to NFN families, NFN+ families would purchase, cook and serve more fruits and vegetables, demonstrate greater utilization of BFF Centers and community resources, and NFN+ infants would be less likely to have a weight for length greater than the 85^th^ percentile. The study protocol was approved by the Institutional Review Board at Connecticut Children’s Medical Center, was sponsored by the Hartford Childhood Wellness Alliance, and was funded by the National Institutes of Health (NICHD R21 HD073966-A01).

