#### Secondary outcome variables

Maternal diet and behavior are being assessed using self- report on maternal fruits, vegetables, and beverage consumption [67]. Mothers are asked how many days per week they eat breakfast, lunch, dinner, and snacks and how many days per week they eat at fast-food or other restaurants. Information about the food and beverages in the home is obtained. The Paffenbarger Health Fitness Assessment is being used to assess maternal activity [68]. Infant weight and length with calculation of the weight for length *z*-score are determined by medical record review at birth, 6 and 12 months.

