### Evaluation plan

Assessments will occur at birth and when the infant is 6 and 12 months. The Family Wellness Plan book is collected at 6 and 12 months and copied and returned to the family. Primary outcomes will be the child’s targeted behaviors at 12 months (i.e., extent and duration of breastfeeding, SSB consumption, timing of introduction of solids, sleep duration and soothability and television viewing) (Fig. 3). Assessed process variables include changes in mothers’ knowledge about dietary recommendations, intentions to make these changes, and self-efficacy to make healthy choices. Six month intermediary variables include changes in the home food environment and mothers’ shopping and cooking practices, child feeding styles, maternal stress, positive parenting practices, and community resource utilization. The RE-AIM analytic framework will be used [72, 73]. For RE-AIM, Reach will be explored by determining the percent of mothers/infants who were excluded and the reasons for exclusion, the percent of eligible mothers/infants who participated, and reasons for dropping out. Effectiveness will be evaluated by comparing differences in maternal behaviors at 6 months between control and intervention mothers and short-term attrition. For Adoption, intervention use (number of doses of each intervention and number of intervention types rendered) and NFN+ worker satisfaction and intention to use the intervention after study’s end will be evaluated. Implementation will be evaluated using the number of completed home visits and the association between these indicators and maternal behaviors. Maintenance will be assessed by examining child behaviors and weight for length *z*-scores at 12 months.

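### The plan labels its weight-for-length test a z-score comparison but runs chi-square on unspecified percentile categories, which serves only one of two differing hypotheses and loses roughly half the information

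*Protocol article*

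**What the plan says.** The article describes this outcome in five places, and they do not agree.

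- **Abstract, Methods/Design:** infants in the intervention arm are expected to have "a lower weight for length *z*-score at 12 months". This is a continuous outcome at one time point.
- **Secondary outcome variables:** infant weight and length, with the z-score calculated from them, "are determined by medical record review at birth, 6 and 12 months". A birth value therefore exists.
- **Evaluation plan:** "Maintenance will be assessed by examining child behaviors and weight for length *z*-scores at 12 months". This is again the continuous score.
- **Overview and hypotheses:** "NFN+ infants would be less likely to have a weight for length greater than the 85^th^ percentile". This is a binary outcome, stated for 6 and 12 months.
- **Statistical analysis plan for secondary outcomes:** the sentence opens "For the comparison of weight for length *z-*score between NFN+ and NFN infants" and ends "weight categories based on weight for length percentiles will be compared using chi-square analysis". It gives no cut-points, number of categories or time point.

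**The concern.** A chi-square test on categories does not compare z-scores. As the sentence stands, the only test named for this outcome carries the label of the continuous hypothesis and can answer only the percentile one. No test is named for the score itself.

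This matters because weight for length is the trial's only measure of infant growth status. It comes from medical records, whereas the primary behaviours come from questionnaires. The Evaluation plan lists worker bias as a threat and prefers objective measures where they are available. The sample is small (49 eligible dyads), so losing information on this outcome is costly. The article already plans t-tests or Wilcoxon tests for its continuous primary outcomes, so a continuous analysis would fit its own methods.

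**Working it through.** **Plan's own figure.** There is none to reproduce for this outcome. The article's only power statement concerns sugar-sweetened drinks, juice and solids before 6 months.

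**Inputs from the article.** 60 participants less 20% dropout gives 48, or 24 per arm. Table 2 has 23 control and 26 intervention dyads. The significance level is 0.05.

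**Assumptions, not in the article.** Normal z-scores with SD 1; no clustering; two-sided test; one cut at the 85th percentile (borrowed from the Overview hypothesis); control mean z (mu) of 0, 0.3 or 0.5; a benefit of 0.5 or 0.8 SD.

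**Step 1: information kept by one cut.** The cut lies at c = 1.036 - mu. The share above it is p = 1 - Phi(c). Relative efficiency is phi(c)^2 / [p(1 - p)].

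| mu | c | p | phi(c) | Kept |
|---|---|---|---|---|
| 0 | 1.036 | 0.150 | 0.233 | 0.43 |
| 0.3 | 0.736 | 0.231 | 0.304 | 0.52 |
| 0.5 | 0.536 | 0.296 | 0.345 | 0.57 |

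First row: 0.233^2 / (0.150 x 0.850) = 0.43.

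**Step 2: other cut-points.** At 80% power, an overall chi-square on several categories keeps 36% (cuts at the 85th and 95th percentiles), 49% (5th and 85th), 44% (5th, 85th and 95th) or 65% (tertiles). A median split keeps 64%. Over all the cuts tried, including single cuts with 15-35% of infants above them, the loss runs from 35% to 64%.

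**Step 3: power at 24 per arm.** The intervention share above the cut is 1 - Phi(c + shift). The chi-square column uses the pooled two-proportion formula, and the means column uses the noncentral t with 46 degrees of freedom.

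| Shift | Shares above the cut, control v intervention (mu = 0; 0.3; 0.5) | Chi-square | Means |
|---|---|---|---|
| 0.5 SD | 0.150 v 0.062; 0.231 v 0.108; 0.296 v 0.150 | 0.16; 0.20; 0.22 | 0.40 |
| 0.8 SD | 0.150 v 0.033; 0.231 v 0.062; 0.296 v 0.091 | 0.28; 0.38; 0.43 | 0.77 |

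A simulation (20,000 runs, 23 v 26, control share above the cut 15-35%) agrees: about 40% against 14-24% at 0.5 SD, and about 78% against 24-48% at 0.8 SD.

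**Step 4: expected counts above the cut.** With no effect, 24p gives 3.6, 5.5 and 7.1 per arm. Under the assumed benefits, the average per arm is 2.2 to 5.3, below 5 in five of the six scenarios. In the simulation with no effect, chi-square rejected in 4.6-5.0% of runs.

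**Step 5: value of the birth score.** Adjustment multiplies the variance by 1 - r^2: 0.96 at r = 0.2 and 0.84 at r = 0.4. At r = 0.4, power for the means comparison goes from 0.40 to 0.46 (0.5 SD) and from 0.77 to 0.84 (0.8 SD). The article does not give r.

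**Step 6: cost of also adjusting for parity.** Table 2 shows 21 of 23 controls and 6 of 26 intervention mothers as primiparous. The correlation with arm is (21 x 20 - 2 x 6) / sqrt(23 x 26 x 27 x 22) = 0.68. The variance inflation is 1 / (1 - 0.68^2), or 1.88 before rounding. Taken together with r = 0.4, power falls from 0.84 to 0.58 (0.8 SD) and from 0.46 to 0.27 (0.5 SD).

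**The case against.** The strongest reply is that the Overview section states a categorical hypothesis and the chi-square tests it. This stands. A reader might infer that the planned test answers no stated hypothesis, and the documents do not support that. What remains is that the article states two endpoints, attaches its one test to the endpoint it cannot serve, and does not commit to the 85th-percentile cut.

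A second reply is that the Evaluation plan still looks at 12-month z-scores and that a condensed article may leave covariates to an analysis plan. In part this stands. Not naming the birth value as a covariate is no fault in itself. However, the article does fix a test, and a plain chi-square has no place for a covariate. The Evaluation plan names no method.

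A third is that the size of the loss rests on inputs that are not in the article. That is right, and it is why ranges are given. Even the unadjusted continuous test has only 0.40 power at 0.5 SD, so the change does not make this outcome well powered.

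A reader might also infer that expected counts invalidate the chi-square. They may fall below 5, but not in every scenario, and the simulated error rate with no effect stayed close to 5%.

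**Conclusion.** The point holds as an inconsistency between stated endpoints, together with an inefficient choice of test for one of them. With one cut at the 85th percentile, normal scores and no clustering, about 43-57% of the information is kept. Power at 24 per arm is roughly 0.3-0.4 where a comparison of means would have 0.77 (0.8 SD), and about 0.2 where it would have 0.40 (0.5 SD). Other cut-points change these figures, and clustering would lower the power of both approaches.

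Two stronger readings are not supported. One is that this is the least efficient test possible: cuts at the 85th and 95th percentiles would keep less. The other is that a fully adjusted model would deliver the whole gain. The birth value helps modestly, by an amount that depends on an unknown correlation, and parity adjustment would take precision away. The outcome is secondary, so the change is advisable and does not bear on the primary comparisons.

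**What to change.** 1. Name the 12-month weight-for-length z-score, analysed as continuous, as the analysis of this outcome. Adjust it for the birth z-score, allow for the centre clustering that the primary analysis section undertakes to control, and report the mean difference with its interval.
2. Keep the proportion above the 85th percentile as a companion measure, with the cut-point and time point stated and an exact test or interval.
3. Align the wording of the hypothesis in the Abstract and in Overview and hypotheses, and say which analysis serves which.
4. If parity is adjusted for, present that as a sensitivity analysis for confounding, since the imbalance inflates the variance about 1.9-fold.

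The cost is wording and a short analysis specification. The birth and 12-month z-scores are already among the planned measurements.

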## Discussion

New models and interventions to prevent childhood obesity and reverse the staggering increases in obesity prevalence over the past 40 years are needed. Interventions need to not only be successful but to also be capable of wide dissemination and implementation at reasonable cost.

The Early Childhood Obesity Prevention Program (ECHO) is a randomized controlled trial testing the efficacy of the early establishment of healthy behaviors in preventing childhood obesity in mothers of Latino and Black children from a low-income, urban community. It is an innovative, ecologically- and culturally-based intervention to obesity prevention. The intervention builds upon an existing home visitation program by incorporating maternal education with skill-building (goa-setting, problem-solving, self-monitoring, and stimulus control). The intervention then uses these core behavioral strategies to target 4 specific areas of behavior change (breastfeeding, delayed introduction of solids, delayed consumption of fruit juice, and infant routines including limiting television/screen time, recognizing cues for hunger and satiety and sleep duration) that mothers are open to change. The intervention has been designed to be incorporated into ongoing home visits which will enhance opportunities for wide dissemination. The intervention is also grounded in Behavior Theory and the Ecological Model of Childhood Obesity to activate mothers to implement new behaviors in the home. The intervention links mothers to community programs and resources, supports maternal changes, and provides feedback on achievement of specific goals determined by the mother within a culturally responsive framework. It also addresses concerns in Latina and Black mothers about weight as a sign of health, breastfeeding, television as an educational tool, and outdoor safety. The study is innovative in its focus on newborns, the use of mothers as agents of change, and the utilization of an existing home visitation program to enhance mother-infant outcomes. The intervention also sets the stage for lasting and endurable change by taking into account the child’s environmental and social milieu and connecting families to neighborhood programs and resources to support behavior change.

## Abbreviations

NFN: Nurturing Families Network
NFN+: Enhanced NFN curriculum
PAT: *Parents as Teachers-Born to Learn*
Partners: *Partners for a Healthy Baby*
SSB: Sugar-sweetened beverages
BFF Center: Brighter Future Family Center
